## Abstract

**Introduction::**

Video-assisted thoracoscopic lobectomy is the prior recommended treatment for non-small cell lung cancer (NSCLC), with the advantages of small trauma, less postoperative pain, and quick recovery. However, a large number of patients may suffer chronic postsurgical pain (CPSP), which makes the patients unwilling to practice pulmonary exercises, and it would directly affect patient's cough, sputum expectoration, and mobility. Opioids could greatly improve the quality of postoperative analgesia and the quality of life after surgery, but it is accompanied with obvious side effects. A number of clinical studies have proved that acupuncture could improve postoperative pain and reduce opioid use. In this study, we try to conduct a randomized controlled study to evaluate the efficacy and safety of plum-blossom needle acupuncture combined with Tramadol in improving CPSP after lobectomy in NSCLC patients.

**Methods::**

Patients will be randomly divided into treatment group (acupuncture plus Tramadol) and control group (sham acupuncture plus Tramadol) with a random number table in 1:1 ratio. The patients, outcome assessor, and statistician will be blinded. The outcomes are changes of numerical rating scale, Karnofsky performance score, brief pain inventory, blood routine, liver and kidney function. The data will be analyzed by SPSS 22.0.

**Conclusions::**

The results will help to evaluate the efficacy and safety of plum-blossom needle acupuncture in improving CPSP after lobectomy in NSCLC patients.

## Introduction

1

Lung cancer is one of the most common malignant tumors, with the highest morbidity and mortality rate worldwide, which seriously threatens human health and life.^[1–3]^ Non-small cell lung cancer (NSCLC) is the major type, and lobectomy is one the effective treatments for early NSCLC.^[4]^ Nowadays, the rapidly emerging technique, video-assisted thoracoscopic lobectomy (VATL) is the prior recommended treatment for NSCLC, with the advantages of small trauma, less postoperative pain, quick recovery, and better patient satisfaction.^[5–8]^ Recently, VATL continues to improve with the decreasing working port size and incisions. The conventional multiportal VATL with several incisions was alternated to triportal, and recently biportal, or even uniportal VATL.^[9,10]^

However, in patients undergoing lobectomy, a large number would suffer chronic postsurgical pain (CPSP), the most common complication after chest surgery. The biportal or uniportal VATL approach has been proposed to perform feasibly and safely in lobectomy with less incisions and quicker recovery, but many patients may still complicate with CPSP.^[11–13]^ The occurrence and severity of CPSP after lobectomy is an important factor to influence the recovery of patients with NSCLC. CPSP makes the patients unwilling to practice pulmonary exercises, and it directly affects patient's cough, sputum expectoration, and mobility. Patient with CPSP may even complicate with atelectasis, lung infection, hypoxemia, which greatly lower the quality of life.^[12,14]^

Conventional analgesia methods for CPSP after lobectomy mainly include patient controlled analgesia, regional analgesia, and analgesic pumps. Patient controlled analgesia, involving opioids such as morphine and fentanyl, as well as anti-inflammatory drugs, could greatly improve the quality of postoperative analgesia and the quality of life after surgery, but it is accompanied with obvious side effects, such as urine retention, vomiting, and allergies. Therefore, to seek a safe and effective combined therapy is important for the treatment of CPSP.

Acupuncture, a traditional alternative therapy, has been used to treat pain for many years,^[15]^ and a number of clinical studies have proved its efficacy for postsurgical pain. Acupuncture could improve postoperative pain and reduce opioid use.^[16]^ However, there are fewer studies on acupuncture against CPSP after lobectomy. Our group preliminarily found that plum-blossom needle percussion, one of the acupuncture therapies in traditional Chinese medicine, combined with analgesic could significantly relieve CPSP in NSCLC patients and reduce the side effects of analgesic. Therefore, in this study, we try to conduct a prospective, randomized controlled study to evaluate the efficacy and safety of plum-blossom needle combined with Tramadol Hydrochloride Sustained Release Tablets in improving CPSP after lobectomy in NSCLC patients.

## Methods

2

### Patients selection

2.1

The randomized, controlled trial will be carried out in Chongqing Steel General Hospital, and it has been approved by the Health Research Ethics Board of Chongqing Steel General Hospital. The study has been registered in open science framework with registration number of DOI 10.17605/OSF.IO/RJEYB. All patients will provide a signed written informed consent at enrollment.

The inclusion criteria for participants are as follows:

(1)diagnosis of CPSP after lobectomy in NSCLC patients;(2)being aged between 35 and 75 years old;(3)with 3 < numerical rating scale (NRS) < 7;(4)with Karnofsky performance score > 60;(5)with signed written informed consent.

Patients will be excluded with the following criteria:

(1)with previous history of thoracic surgery;(2)who had undergone targeted therapy or chemoradiotherapy before;(3)with peripheral structures invasion;(4)with contraindication plum-blossom needles, such as wounds, ulcers, scars at the puncture site;(5)with abnormal renal or liver function;(6)with other surgical contradictions.

### Randomization and blinding

2.2

Patients will be randomly divided into treatment group (acupuncture plus Tramadol) and control group (sham acupuncture plus Tramadol) with a random number table in 1:1 ratio (Fig. 1). To maintain blinding, patients in both groups will be performed plum-blossom needles percussion. In the treatment group, the plum-blossom needles will be stick on the pain area, while in the control group, the needles will be performed around the pain area as sham acupuncture. The patients, outcome assessor, and statistician will be blinded.

**Figure 1 F1:**
[figure not shown]
Flow diagram.

### Interventions

2.3

Patients with CPSP in both groups will take Tramadol Hydrochloride Sustained Release Tablets (Shandong Xinhua Pharmaceutical Company Limited, H19990062), 100 mg, and twice a day for 14 days.

In the treatment group, plum blossom needles (Gushi Medical Instrument Co., LTD, 20192200580) percussion will be performed on pain area, 70 to 90 times per minute for 10 minutes, with moderate percussion intensity, once every 2 days, and the treatment course will be 14 days.

While in the control group, plum blossom needles (Gushi Medical Instrument Co., LTD, 20192200580) percussion will be performed around the pain area, 70 to 90 times per minute for 10 minutes, with moderate percussion intensity, once every 2 days, and the treatment course will be 14 days.

### Outcome measures

2.4

The primary outcome is the change of NRS at day 0, day 7, and day 14. The secondary outcomes are Karnofsky performance score, brief pain inventory, blood routine, liver and kidney function before and after the treatment. The change of Tramadol application will be recorded. All adverse events will be also recorded.

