### Sample size

2.5

In our preliminary trial, the changes of NRS in treatment group and control group are 2.65 ± 1.25 and 1.8 ± 1.31, respectively. Taking α = 0.05, β = 0.2, 30 cases will be needed in each group. Considering a loss to follow-up of 20%, the estimated sample size will be 72.

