### Statistical methods

2.6

The data will be analyzed by SPSS 22.0 (IBM, Chicago). The count data will be described by number and percentages, and the comparison between groups will be performed by chi-square test; The measurement data will be presented as mean ± standard deviation. Repeated measures analysis of variance will be applied for repeated data, considering normality and homogeneity. For the changes between groups, *t* test or Mann–Whitney *U* test will be applied accordingly. *P* < .05 will be considered statistically significant.

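### No single day or contrast is named as primary for NRS change; if either day 7 or day 14 may count as success, the false-positive rate is about 9%, not 5%

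*Protocol article*

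**What the plan says.** Protocol article, section 2.4 (Outcome measures): "The primary outcome is the change of NRS at day 0, day 7, and day 14". No day, average or trend is singled out. The secondary outcomes are taken before and after treatment.

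Section 2.6 (Statistical methods) describes two routes to a between-group P value. The first is: "Repeated measures analysis of variance will be applied for repeated data, considering normality and homogeneity". The model effect that answers the trial's question is not named. The second is: "For the changes between groups, *t* test or Mann–Whitney *U* test will be applied accordingly". The day of the change is not named. Any P below .05 "will be considered statistically significant". No order of testing or adjustment is given.

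Section 2.5 (Sample size) uses one pair of pilot figures: "the changes of NRS in treatment group and control group are 2.65 ± 1.25 and 1.8 ± 1.31, respectively". It continues: "Taking α = 0.05, β = 0.2, 30 cases will be needed in each group". It states neither the day of the change nor whether alpha is one- or two-sided.

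Section 2.3 (Interventions) sets a treatment course of 14 days, so day 14 is the end of treatment.

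**The concern.** The outcome, analysis and sample-size sections should all point to the same hypothesis, and here they do not. The outcome section leaves two days on an equal footing, the analysis section gives more than one kind of test, and the sample size assumes a single contrast with no date.

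Once results are known, a day-7 difference, a day-14 difference or a group-by-time interaction could each be reported as the primary result, and each would be consistent with the text. A reader could not tell a prespecified success from a selected one. If the choice is made among several tests, the 5% used for sizing is no longer the error rate of the trial's claim.

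**Working it through.** **Inputs from the article.** Pilot changes 2.65 and 1.8, SDs 1.25 and 1.31, alpha 0.05, power 0.80, 30 per group (section 2.5); threshold P < .05 (section 2.6); days 0, 7 and 14 (section 2.4).

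**Assumptions.** The article gives no correlations between days, so these are assumed and a range is shown. The error-rate calculations take each test as two-sided at 0.05.

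**1. The plan's own sample size.**
- Difference: 2.65 − 1.8 = 0.85.
- Pooled SD: √((1.25² + 1.31²)/2) = √1.6393 = 1.280.
- Formula: n per group = 2 × SD² × (z_alpha + z_power)² / difference².
- One-sided 0.05: 2 × 1.6393 × (1.645 + 0.842)² / 0.7225 ≈ 28.1, so 29. With the larger SD of 1.31 it is 30, which matches the plan.
- Two-sided 0.05: 2 × 1.6393 × (1.960 + 0.842)² / 0.7225 ≈ 35.6, so 36 (37 by noncentral t).
- With 30 per group and a two-sided 0.05 test, power is 73% by normal approximation and 72% by noncentral t.

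The figure of 30 is reproduced only for a single one-sided contrast.

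**2. How many changes can be tested.** Change at day 0 is zero for every patient, so the changes are day 7 minus day 0 and day 14 minus day 0. The *t* test and Mann–Whitney test are alternatives, so they add no further test. Two tests remain, not three.

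**3. Correlation between the two changes.** They share a baseline. With equal variances and a common within-patient correlation r, their covariance is proportional to 1 − r and each variance to 2(1 − r). Their correlation is therefore 0.5 whatever r is. Other patterns would give other values.

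**4. Error rate if either day may count.** This is 1 − P(|Z₁| < 1.96 and |Z₂| < 1.96), with (Z₁, Z₂) bivariate normal.

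| Assumed correlation of the two changes | Either day significant |
|---|---|
| 0 (upper bound, 1 − 0.95²) | 9.75% |
| 0.3 | 9.5% |
| 0.5 | 9.1% |
| 0.7 | 8.3% |
| 0.8 | 7.8% |
| 0.9 | 7.0% |

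**5. Simulated null trial.** 30 per group, days 0, 7 and 14, within-patient correlation 0 to 0.7 (assumed), 20,000 runs for each value.

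| What counts as success | False-positive rate |
|---|---|
| Day-14 change only | 4.9–5.1% |
| Group-by-time test only | 4.8–5.0% |
| Day 7 or day 14 | 8.8–9.2% |
| Day 7, day 14 or group-by-time | 9.7–10.1% |

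If both days had to be significant, the rate at correlation 0.5 would be 5% + 5% − 9.1% = 0.9%, about 1%.

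**6. Cost of keeping both days primary.** With Bonferroni at two-sided 0.025: 2 × 1.6393 × (2.241 + 0.842)² / 0.7225 ≈ 43.1, so 44 per group before losses. The planned 30 would have about 63% power (normal approximation).

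**The case against.** **The inflation is conditional.** A reader might infer that the false-positive rate simply exceeds 5%. The article does not support that. It is silent on the decision rule, and silence is not a rule that any significant test wins. If one contrast decides, the rate is about 5%; if both days are required, it is about 1%. This objection stands, and the 9% must carry its condition.

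**A single-test reading is possible.** The three days can be read as a measurement schedule. NRS is the only outcome listed at three days, so the repeated measures analysis could be meant for it, and the tests of change for the before-and-after secondary outcomes. But the sample size is built on a between-group NRS change, which points to the other test, and even on this reading the deciding model effect is not named. The reading is plausible but not settled by the text.

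**Larger figures do not hold up.** Counting three time points as independent tests gives 14.3%, but day 0 offers no change to test. Adding the group main effect of the repeated measures analysis gives about 14% in the same simulation. That effect averages in the pre-treatment day and is not a test of change, which is how the primary outcome is defined.

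**An article is condensed.** Model details and the order of secondary tests can properly sit in a full protocol or SAP that is not shown. That does not remove the point. The article does define its primary outcome, and the definition lists a day with no change and leaves two others equally primary. The contrast for which the trial is sized belongs with that definition.

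**Conclusion.** The point holds in this limited form. Without any condition, the article names no single day or contrast as primary, and the day behind the sample-size difference is unstated. Conditionally, if significance on either day 7 or day 14 may count as success, the false-positive rate is about 9% (7.8–9.5% for assumed correlations of 0.8 to 0.3), and about 10% if the group-by-time test may also count. The text permits that use but does not state it, so it cannot be said that the trial's error rate is above 5%. The figures rest on two-sided 0.05 tests, approximate normality and correlations that the article does not supply.

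**What to change.** In section 2.4, name one primary contrast. An example is the between-group difference in NRS change from day 0 to day 14, the end of the treatment course, tested once at the stated alpha. Make day 7 and the repeated-measures time-course tests secondary. Day 14 is one acceptable choice; what matters is that one contrast is fixed before the data are seen.

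In section 2.5, state which day the 0.85 difference refers to and whether alpha is one- or two-sided. If the test is two-sided 0.05, correct the stated power: 30 per group gives about 72% on the plan's own inputs.

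The cost is a few sentences. Naming one contrast adds no patients, because the sample size already assumes only one. Restoring 80% power under a two-sided test would need more, 36 to 37 per group before losses. The downside is that an effect seen only on day 7 could no longer be claimed as the primary result.

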### Sample size

2.5

In our preliminary trial, the changes of NRS in treatment group and control group are 2.65 ± 1.25 and 1.8 ± 1.31, respectively. Taking α = 0.05, β = 0.2, 30 cases will be needed in each group. Considering a loss to follow-up of 20%, the estimated sample size will be 72.

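### Section 2.5 does not say whether alpha is one- or two-sided: 30 per group fits only a one-sided 5% test, and under the usual two-sided reading of section 2.6 it gives about 72% power, not 80%

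*Protocol article*

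**What the plan says.** Section 2.5 (Sample size) takes its assumptions from a preliminary trial: "the changes of NRS in treatment group and control group are 2.65 ± 1.25 and 1.8 ± 1.31, respectively". From these it concludes: "Taking α = 0.05, β = 0.2, 30 cases will be needed in each group". It then allows for attrition: "Considering a loss to follow-up of 20%, the estimated sample size will be 72". Section 2.2 allocates patients "with a random number table in 1:1 ratio".

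Section 2.6 (Statistical methods) describes the analysis. "Repeated measures analysis of variance will be applied for repeated data", and "For the changes between groups, *t* test or Mann–Whitney *U* test will be applied accordingly". One threshold, P < .05, "will be considered statistically significant" for all tests.

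Neither section mentions sidedness, and section 2.5 names no formula.

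**The concern.** A sample-size section that prints two means, two SDs, alpha, beta and a result can be checked. Here the printed result is clearly smaller than these inputs give for the test most readers would assume. If the calculation was one-sided and the analysis is two-sided, the two sections do not match, and the stated 20% type II error does not apply to the test that will be run.

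The consequence is a risk of missing a real effect that is larger than stated. A true difference of 0.85 points on the NRS would be missed in about 28% of such trials rather than 20%. Anyone weighing a non-significant result against the stated 80% power would give it more weight than it deserves.

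**Working it through.** **Inputs**
- Difference in mean NRS change: 2.65 − 1.80 = 0.85 (section 2.5).
- SDs 1.25 and 1.31 (section 2.5). The sum of variances is 1.5625 + 1.7161 = 3.2786, the pooled SD is √(3.2786/2) = 1.280, and the standardised difference is 0.85/1.280 = 0.664.
- Alpha 0.05 and beta 0.2 (section 2.5).
- Allocation 1:1 (section 2.2).
- Sidedness: not stated, so both cases are computed.

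**Formula.** For two means by the normal approximation, n per group = (SD₁² + SD₂²)(z_alpha + z_beta)² / difference². The t-test figures use the noncentral t distribution.

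**Step 1: reproduce the plan's 30 (one-sided 5%)**
- Normal: 3.2786 × (1.645 + 0.8416)² / 0.7225 = 28.1, so 29.
- t test: 28.8, so 29.
- With SD 1.31 in both groups, normal: 29.4, so exactly 30.
- With the pooled SD and the usual large-sample allowance for a Mann–Whitney test (divide by 0.955): 28.76/0.955 = 30.1.
- Power with 30 per group and the pooled SD: 82.3% (normal) or 81.5% (t test).

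A one-sided 5% test therefore reproduces the printed number.

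**Step 2: the same inputs, two-sided 5%**
- Normal: 3.2786 × (1.960 + 0.8416)² / 0.7225 = 35.6, so 36.
- t test: 36.6, so 37.

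| SD used | n per group, normal | n per group, t test | Power at 30 per group, t test |
|---|---|---|---|
| 1.25 | 34 | 35 | 73.6% |
| 1.280 (pooled) | 36 | 37 | 71.5% |
| 1.31 | 38 | 39 | 69.5% |

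No choice of SD within the printed values brings a two-sided requirement down to 30. By the normal formula, power at 30 per group with the pooled SD is 72.9%. The standard error is 1.280 × √(2/30) = 0.331, then 0.85/0.331 = 2.57 and 2.57 − 1.96 = 0.61.

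**Step 3: what 30 per group can detect with 80% power, two-sided**
- Normal: (1.960 + 0.8416) × 0.331 = 0.93.
- t test: about 0.94.

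**Step 4: full retention of the 72 (36 per group), two-sided**
- Normal: 80.4%.
- t test: 79.3%.

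**The case against.** The strongest defence is that two-sidedness is nowhere stated. A one-sided 5% test is a legitimate reading of the bare figure for alpha, and under it 30 per group gives about 82% power. This stands. A reader might infer that the 30 is an arithmetic slip, or that the plan's own inputs cannot give 80% power. The document does not support that: the number follows from the inputs once alpha is taken as one-sided.

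The defence does not remove the mismatch with section 2.6. An ANOVA F test has no direction. A t, Mann–Whitney or chi-square test judged at an unqualified P < .05 is two-sided by convention. The stated aim is to evaluate efficacy and safety, with no directional hypothesis declared.

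A second defence is that this is a condensed article, and a fuller document may give the formula and the sidedness. That would excuse silence on its own. Here, though, the article prints its inputs and its result, and no two-sided variant connects them.

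A third defence is that the enrolment of 72 nearly meets the two-sided requirement if nobody is lost (79.3% by t test, 80.4% by the normal formula). This also stands, so a reader should not infer that enrolling 72 is far too few under any circumstances. But section 2.5 itself expects 20% loss and rests its power claim on 30 evaluable patients per group. The shortfall arises at that number.

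**Conclusion.** The point holds in this form: section 2.5 leaves the sidedness of alpha unstated, and its 30 per group is consistent only with a one-sided 5% test, while section 2.6 plans analyses that are non-directional or two-sided by convention. If the analysis is two-sided, 36 to 37 evaluable patients per group are needed for 80% power. Thirty give about 72% (70% to 74% across the printed SDs), a type II error of about 28% instead of 20%.

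This rests on three assumptions: the pilot difference and SDs are taken at face value, the primary comparison is a two-group comparison of mean change, as the section 2.5 inputs imply, and the tests in section 2.6 are run two-sided. The last is an inference from the tests named and from convention, not a stated input. It would be wrong to report flatly that 30 per group cannot give 80% power. What can be said is that it does not do so for the analysis as it would ordinarily be read.

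**What to change.** State in sections 2.5 and 2.6 that tests are two-sided at 0.05. Restate section 2.5 along these lines: with 30 evaluable patients per group and an SD of 1.28, the trial has about 72% power for a difference of 0.85 in NRS change, or 80% power for a difference of about 0.94. It would help to add that 80% power for 0.85 would need 37 evaluable per group by the t test.

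Do not declare a one-sided 5% test to keep the number. It would allow twice the chance of a false positive in the favoured direction (5% instead of 2.5%), and it would not fit the planned ANOVA.

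The cost is a few corrected sentences and a less favourable stated power. No extra patients are required if the power is restated.

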### Statistical methods

2.6

The data will be analyzed by SPSS 22.0 (IBM, Chicago). The count data will be described by number and percentages, and the comparison between groups will be performed by chi-square test; The measurement data will be presented as mean ± standard deviation. Repeated measures analysis of variance will be applied for repeated data, considering normality and homogeneity. For the changes between groups, *t* test or Mann–Whitney *U* test will be applied accordingly. *P* < .05 will be considered statistically significant.

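### Blood, liver and kidney values fall under a rule of mean ± SD with a t or Mann–Whitney test, which will usually miss one to three patients with severe new abnormalities; a count per arm would show them

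*Protocol article*

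**What the plan says.** Safety is part of the stated aim: the Introduction says the trial will "evaluate the efficacy and safety of plum-blossom needle combined with Tramadol Hydrochloride Sustained Release Tablets".

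The laboratory values enter in section 2.4 (Outcome measures): "The secondary outcomes are Karnofsky performance score, brief pain inventory, blood routine, liver and kidney function before and after the treatment". The same section adds "All adverse events will be also recorded".

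Section 2.6 (Statistical methods) sorts the data into two kinds. For counts: "The count data will be described by number and percentages, and the comparison between groups will be performed by chi-square test". For numeric data: "The measurement data will be presented as mean ± standard deviation". For change scores: "For the changes between groups, *t* test or Mann–Whitney *U* test will be applied accordingly". The significance criterion is P < .05. The section does not mention the laboratory variables by name and does not say how they would become counts.

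Section 2.1 (Patients selection), exclusion 5, rules out patients "with abnormal renal or liver function". It does not mention blood counts. Section 2.3 (Interventions) gives both arms the same tramadol product, dose and duration; the arms differ only in whether the needle is applied on or around the painful area.

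**The concern.** Laboratory results measured before and after treatment are numeric, so on a plain reading they follow the measurement-data rule: a mean and SD per arm and a t or rank test of the changes. Laboratory harm in a trial of this size would typically appear as a few extreme values, not as a shift of the whole group. A few extreme values inflate the SD in the denominator of the t statistic and hardly move the ranks, so neither test is likely to react. Both arms also take the same drug, so harm from it would be expected in both, and a comparison between arms is not built to reveal that.

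At stake is false reassurance on the safety aim: a table of similar means with a non-significant P value while individual patients have clearly abnormal results. The primary pain outcome is not affected.

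**Working it through.** **1. Number of patients behind each laboratory mean.** Section 2.5 states 30 per group and 72 in total. Inputs: NRS changes 2.65 ± 1.25 and 1.8 ± 1.31, α = 0.05, β = 0.2.
- Difference = 2.65 − 1.8 = 0.85. Pooled variance = (1.25² + 1.31²)/2 = 1.639, so SD = 1.280.
- n per group = 2 × (z_α + z_β)² × SD²/difference². One-sided: 2 × (1.645 + 0.842)² × 1.639/0.7225 = 28.1, so 29. Two-sided: 2 × (1.960 + 0.842)² × 1.639/0.7225 = 35.6, so 36.
- The stated 30 is close to the one-sided result only. That does not affect the present point, which needs only the arm size. 60 × 1.2 = 72 gives 36 per arm recruited, and 30 per arm is the target without losses.

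**2. Assumptions.** The article gives no laboratory figures, so these are illustrative: a liver enzyme with baseline mean 25 U/L and upper normal limit 40 U/L; change with mean 0 and SD 8 in unaffected patients; affected patients rise to 120–200 U/L (3 to 5 times the limit), an average rise of 160 − 25 = 135.

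**3. Why the t test does not react (36 per arm, 2 affected v 0).**
- Shift in mean change = 2 × 135/36 = 7.5 U/L.
- Variance in the affected arm ≈ 8² + (2 × 34/36) × 135²/35 ≈ 64 + 984 = 1,048, so SD ≈ 32 instead of 8.
- Standard error of the difference = √((1,048 + 64)/36) = 5.56, so the typical t = 7.5/5.56 = 1.35, below the critical value of 1.99 on 70 degrees of freedom.

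**4. Why Mann–Whitney does not react.** The probability that a patient in the affected arm exceeds one in the other is about (34/36) × 0.5 + 2/36 = 0.528, against 0.5 under no effect. Its standard error is √(73/(12 × 36 × 36)) = 0.0685, so the typical z is 0.028/0.0685 = 0.41.

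**5. Simulation.** Share of trials with P < .05:

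| Affected (one arm v other) | Setting A: t | Setting A: Mann–Whitney | Setting B: t | Setting B: Mann–Whitney |
|---|---|---|---|---|
| 1 v 0 | 1.1% | 5.1% | 0% | 5% |
| 2 v 0 | 3.1% | 6.1% | 0.2% | 5% |
| 3 v 0 | 15.0% | 7.3% | 9% | 8% |

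Both settings have 36 per arm. Setting A uses the assumptions in step 2. Setting B takes baseline SD 8, change SD 6 and every affected patient at 200 U/L. With 30 per arm, setting B gives 0%, 0.1% and 9% by t test, and 5%, 7% and 9% by Mann–Whitney.

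**6. Harm in both arms.** With 2 affected in each arm the expected difference in mean change is 7.5 − 7.5 = 0, so there is nothing for a between-arm test to detect.

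**7. What a count shows.** Two of 36 is 5.6%, with an exact (Clopper–Pearson) 95% interval of 0.7% to 18.7%. As a test it is not significant either: at 36 per arm Fisher P = 0.49 for 2 v 0 and 0.24 for 3 v 0. P < .05 needs 4 v 0 by uncorrected chi-square (P = 0.040) or 6 v 0 by Fisher (P = 0.025).

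**The case against.** The strongest reply is that this is detail a condensed article leaves to the full protocol or analysis plan. That holds for abnormality thresholds, shift tables and listings, and their absence is no finding. The point is narrower: section 2.6 does state a summary and a test for numeric data, and for these outcomes the stated choice is a poor one.

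A reader might infer that the trial will judge safety by these tests and call a non-significant result safe. The article does not say so. Section 2.6 never names the laboratory variables, its rule for counts could carry a normal/abnormal table, and adverse events are recorded separately. A severe value might be caught there, although nothing says that laboratory values will be graded as events.

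A reader might also infer from exclusion 5 that any abnormal value after treatment is new. That follows for liver and kidney function only; blood counts are not covered.

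Three further objections stand in part. The count has little power at this size, so its benefit is display. The mean ± SD table is not wholly blind: in the example the SD rises about fourfold, which an alert reader would notice, though it would not show how many patients were affected or how badly. And because both arms take the same tramadol course, a 2 v 0 split in drug-related harm would most likely be chance; but this also counts against relying on a between-arm test.

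**Conclusion.** The point holds as a weakness in the stated rule. Laboratory values fall under mean ± SD with a t or Mann–Whitney test, and with 30 to 36 patients per arm that rule will usually miss one to three patients with severe new abnormalities. In the settings tried, P < .05 occurred in 0% to 15% of trials by t test and 5% to 9% by Mann–Whitney, mostly near or below the 5% expected by chance. For 2 v 0 under the main assumptions (setting A) the figures are about 3% and 6%. Harm common to both arms is not detectable by such a test.

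The percentages rest on assumed enzyme values; the mechanism (inflated SD, almost unchanged ranks) does not depend on their exact size. That these tests govern the laboratory values is an inference, though the natural one. The documents do not support saying that the safety question would be answered wrongly, only that the stated summary could give false reassurance. The change is worth making; it does not touch the primary outcome.

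**What to change.** In section 2.6 add, for each liver and kidney variable and per arm, the number and percentage of patients who move from normal before treatment to abnormal after it, with exact confidence intervals. Exclusion 5 means that all eligible patients should start normal on these. For blood counts, give the same table among patients whose baseline value is normal. Keep means and SDs as description, and state that safety will not be inferred from a non-significant P value.

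The cost is one table and about two sentences, from data already collected. The small downside is that trivial excursions just outside the reference range will also be counted. The table makes affected patients visible; it should not be presented as a more powerful test.

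### No analysis named for NRS adjusts for the day-0 score that the trial collects; ANCOVA would be at least as precise, apart from one degree of freedom, at almost no cost

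*Protocol article*

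**What the plan says.** Section 2.4 (Outcome measures) defines the primary outcome: "The primary outcome is the change of NRS at day 0, day 7, and day 14". Day-0 NRS is therefore available for every randomised patient. Section 2.1 (Patients selection) limits entry to patients "with 3 < numerical rating scale (NRS) < 7".

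Section 2.6 (Statistical methods) contains two sentences that could apply to NRS. One reads "Repeated measures analysis of variance will be applied for repeated data, considering normality and homogeneity". The other reads "For the changes between groups, *t* test or Mann–Whitney *U* test will be applied accordingly". The section does not say which of the two is the primary analysis of NRS, and neither names a baseline covariate. No baseline-adjusted model appears elsewhere in the article.

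Section 2.5 (Sample size) rests on group means of change: "the changes of NRS in treatment group and control group are 2.65 ± 1.25 and 1.8 ± 1.31, respectively". It then states "Taking α = 0.05, β = 0.2, 30 cases will be needed in each group".

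**The concern.** A test of change scores subtracts the whole baseline value, which fixes the slope of follow-up on baseline at 1. Pain scores carry measurement noise and regress to the mean, so the true slope is usually below 1. The change score then keeps baseline noise that a regression on baseline would remove. Repeated measures ANOVA with day 0 among the responses does not remove it either. With day 0 and one follow-up, its group-by-time test is equivalent to the change-score t test.

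What is at stake is precision on the primary outcome of a small trial. If testing is two-sided, 30 per group gives less than the stated 80% power (shown under the working), so a gain that needs no extra patients is worth having.

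**Working it through.** **Inputs from the protocol.** Mean changes 2.65 and 1.8, difference 0.85; SDs of change 1.25 and 1.31; α 0.05; β 0.2; 30 per group (section 2.5). Entry NRS above 3 and below 7 (section 2.1).

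**Inputs assumed.** The baseline SD and the slope (or correlation) are not given. If scores are integers spread evenly over 4, 5 and 6, the baseline variance is 2/3 and the SD is 0.82. Integer scores of 4 to 6 cannot have an SD above 1.0. The slope is shown as a range.

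**Step 1: the plan's own figure.** The pooled variance of change is (1.25² + 1.31²)/2 = 1.639, SD 1.28. The standard two-means formula gives n per group = 2 × 1.639 × (z_α + z_β)²/0.85².
- One-sided 0.05: 2 × 1.639 × (1.645 + 0.842)²/0.7225 = 28.1, so 29. With SD 1.31 it is 30. The stated 30 reproduces.
- Two-sided 0.05: 2 × 1.639 × (1.960 + 0.842)²/0.7225 = 35.6, so 36 (37 by noncentral t). The stated 30 does not reproduce.

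The protocol does not state sidedness. Two-sided power of the unadjusted t test with 30 per group is 71.5% by noncentral t.

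**Step 2: what adjustment saves.** Let V be the variance of change, s₀² the baseline variance, s₁² the day-14 variance and b the slope of day-14 NRS on day-0 NRS. Then

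V = s₀² + s₁² − 2·b·s₀²

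ANCOVA residual variance = s₁² − b²·s₀² = V − (1 − b)²·s₀²

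The saving is (1 − b)²·s₀². It is never negative; the only charge is one degree of freedom.

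**Step 3: numbers.** With s₀² = 0.667 and V = 1.639, each assumed day-14 SD implies b = (0.667 + s₁² − 1.639)/(2 × 0.667). Power is two-sided with 30 per group.

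| Day-14 SD | Slope b | Saving (1 − b)² × 0.667 | Residual variance | Reduction | Power |
|---|---|---|---|---|---|
| 1.2 | 0.35 | 0.281 | 1.358 | 17% | 79% |
| 1.3 | 0.54 | 0.142 | 1.497 | 9% | 75% |
| 1.5 | 0.96 | 0.001 | 1.638 | about 0% | 71.5% |

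Using 57 instead of 58 degrees of freedom changes these powers by less than 0.1 percentage point.

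**Step 4: dependence on the baseline SD.** At slope 0.5 the saving is 0.25·s₀². With SD 0.82 this is 0.167, or 10% of 1.639. With SD 0.5 it is 0.0625, or about 4%. A narrow entry range makes s₀² small and so limits the gain.

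**Step 5: the choice between t and Mann–Whitney.** In simulations of no effect with 30 per group (normal, rounded normal and skewed data), choosing the test by a Shapiro–Wilk pretest gave a type I error of 4.7% to 5.1%. Reporting the smaller of the two p-values gave 5.3% to 6.3%, but the protocol does not propose that.

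**The case against.** The strongest reply is that the planned tests are valid under randomisation, that the change score matches the basis used for sizing, and that the gain may be close to nil. All of this stands. It makes the point an improvement in efficiency and not the correction of an error.

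It is also fair that NRS, as the only outcome with three stated time points, may be meant for repeated measures ANOVA, with the t or Mann–Whitney test serving the outcomes taken before and after treatment. The power figures above describe a change-score comparison at one follow-up, which the article does not clearly name as primary. The point survives because neither method adjusts for day-0 NRS.

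Four stronger readings are tempting, and the documents do not support them:
- *The narrow entry range pushes the slope well below 1.* Selecting on baseline does not change a linear slope. It reduces the baseline variance, and with it the gain from ANCOVA.
- *The test is settled once the result is known.* The wording follows a reference to normality and homogeneity, so the choice turns on distribution and not on the treatment comparison. A formal pretest leaves the type I error near 5%.
- *Chance baseline imbalance is a further harm.* With 30 per group its 95% range is 1.96 × 0.816 × √(2/30) = ±0.41 points, which at slope 0.35 moves the change-score estimate by up to 0.65 × 0.41 = 0.27. That movement is already part of the change-score standard error (95% half-width about 1.96 × 1.28 × √(2/30) = 0.65), so it is the same variance counted again.
- *The gain could be 39% of the variance, with power of 90%.* That needs a day-14 SD of 1.0, which implies a correlation of about 0.02 between baseline and day-14 pain. It is an extreme case and should not be the headline.

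**Conclusion.** The point holds as a free improvement. The protocol collects day-0 NRS and names no analysis that uses it as a covariate. ANCOVA would be at least as precise, apart from one degree of freedom. With an assumed baseline SD of 0.82 and slopes of about 0.35 to 0.95, the residual variance falls by about 17% to 0%, and power goes from about 71.5% to between 79% and 71.5%. These powers assume two-sided testing at 0.05, 30 analysed patients per group, and the pilot difference and SDs. The size of the gain cannot be fixed from the document, because neither the baseline SD nor the slope is reported. The planned unadjusted analyses remain unbiased and valid.

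**What to change.** In section 2.6, name one primary analysis of NRS that includes day-0 NRS as a covariate. Two forms would do:
- ANCOVA of day-14 NRS, or of its change from day 0, on treatment group and day-0 NRS, once the sponsor has confirmed that day 14 is the primary time point. With day-0 NRS in the model, either outcome gives the same treatment estimate.
- A repeated measures model of the day-7 and day-14 scores, with treatment group, time and their interaction, and day-0 NRS as covariate.

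Report the adjusted mean difference with its 95% CI whatever a normality check shows, and keep the Mann–Whitney test as a sensitivity analysis. Treat the brief pain inventory and Karnofsky score in the same way, with their own pre-treatment values as covariates.

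The cost is a sentence or two. The data are already collected, SPSS 22.0 can fit the model, and the only statistical charge is one degree of freedom.
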